### Sample Size

The sample size calculation is based on our previous clinical research in patients with cervical spondylosis of the nerve root type, using the same primary outcome instrument. The efficiency of SCRM is 89.5%, while that of BCM is 54.6%. The sample size calculation formula is as follows:

The α is .05 and 1–β is .90. According to estimations, 48 participants per group are needed considering that this is a long-term follow-up that is expected to have a dropout rate of no greater than 20%.

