#### Primary Outcome

##### Efficacy Rate

The clinical symptoms of all subjects will be recorded and evaluated using the numerical rating scale (NRS), which is composed of a horizontal line having a length from 0 to 10 cm, with “0” indicating “normal” and “10” indicating “unbearable.” We will refer to the efficacy evaluation standards in the “Diagnostic and Therapeutic Efficacy Standards for Traditional Chinese Medicine Diseases” issued by the China Administration of Traditional Chinese Medicine in 1994.

We define clinical cure as a decrease of more than 80% in the NRS score for clinical symptoms and the ability to live and work normally. We define clinical improvement as a decrease of 20% to 80% in the NRS score for clinical symptoms. We define clinical cureless as a decrease of less than 20% in the NRS score for clinical symptoms. We define clinical recurrence as the reappearance of the original symptoms after treatment, with the degree being equivalent to or greater than that before treatment.

All patients will be followed up, and the efficacy rate will be calculated at visit 1 after the intervention. The efficacy rate and clinical recurrence rate will be calculated at visit 6. The calculation formulas are as follows:

Efficacy rate = ([number of clinical cure cases + number of clinical improvement cases – number of clinical cureless cases] / total number of patients) 100

Clinical recurrence rate = (number of clinical cureless cases / [number of clinical cure cases + number of clinical improvement cases]) 100

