### Statistical Analysis

The main objective of this study is to evaluate the clinical effectiveness of SCRM therapy in patients with AJS. Additionally, secondary analyses will be conducted to assess changes in VAS scores, VSS-C scores, imaging findings, and cervical mobility before and after treatment in patients with AJS. Analyses will be performed using IBM SPSS 22.0. The measurement data will be expressed using mean differences (mean and standard deviation). The repeated measurement data will be analyzed using within-group variance analysis. Enumeration data will be presented as rates. The sample size needed for the Pearson chi-square test to compare rates between the 2 groups before and after treatment will be determined using the normal approximation algorithm and a 1-sided test. This study employs the superiority test that uses a 1-sided test level of α=.05. A *P* value of ≤.05 signifies the rejection of H0, thereby establishing the superiority of the SCRM group over the BCM group. Conversely, a *P* value >.05 indicates that a definitive conclusion regarding superiority cannot be drawn at this stage. The safety analysis will employ the chi-square test to compare the incidence of adverse reactions between the 2 groups. In instances where the data fail to meet the requirements of the chi-square test, the Fisher exact probability method will be employed.

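### The recurrence rate is divided by responders only, so comparing it between arms is not protected by randomisation; read literally, the printed formula is not a recurrence rate at all

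*Protocol article*

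**What the plan says.** All of the following stands under the primary outcome in the protocol article, section Efficacy Rate, unless another section is named.

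- **Formula.** "Clinical recurrence rate = (number of clinical cureless cases / [number of clinical cure cases + number of clinical improvement cases]) 100"
- **Its denominator.** "number of clinical cure cases + number of clinical improvement cases]) 100"
- **Numerator category.** "We define clinical cureless as a decrease of less than 20% in the NRS score for clinical symptoms"
- **Recurrence in words.** "We define clinical recurrence as the reappearance of the original symptoms after treatment, with the degree being equivalent to or greater than that before treatment"
- **Timing.** "The efficacy rate and clinical recurrence rate will be calculated at visit 6". The visit at which the denominator is counted is not given.
- **Contrast.** The efficacy rate ends in "number of clinical cureless cases] / total number of patients) 100", so it is taken over all patients.
- **Test.** The Statistical Analysis section refers to a "Pearson chi-square test to compare rates between the 2 groups before and after treatment", in a sentence whose subject is the sample size. It sets a one-sided superiority test and does not mention recurrence.
- **Planned rates.** The Sample Size section states: "The efficiency of SCRM is 89.5%, while that of BCM is 54.6" (per cent).

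**The concern.** Whether a patient is cured or improved is decided after randomisation, partly by the technique received. If recurrence is counted among those patients, the arms contribute different kinds of patients to the comparison. At the planned rates the SCRM denominator would include about 35 patients per 100 who would not have responded to BCM. If these extra responders are harder to treat, SCRM can show the higher recurrence rate although it makes no patient relapse more. If they are easier to keep well, the distortion runs the other way.

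What is at stake is any statement at week 24 about which technique gives the more lasting benefit. Correcting only the numerator or the visit would leave this problem in place.

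**Working it through.** **Inputs from the protocol.** Response 0.895 (SCRM) and 0.546 (BCM), and 48 per group, all from Sample Size. No expected recurrence rate is stated, so there is no planned recurrence figure to reproduce.

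**Reading 1: the formula as printed, all counts at visit 6.** If every patient is classed as cured, improved or cureless, and p is the share cured or improved, the formula equals (1 − p)/p.

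- SCRM: 0.105/0.895 = 11.7%.
- BCM: 0.454/0.546 = 83.2%.
- In whole patients at 48 per arm: 5/43 = 11.6% and 22/26 = 84.6%.
- At p = 0.30: 0.70/0.30 = 233%.

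Cureless patients are outside the denominator, so this is an odds of non-response and not a proportion of responders. It falls whenever p rises, so it always ranks the arms as the response rate does. It also counts patients who never responded, and they cannot have relapsed.

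**Reading 2: recurrence as defined in words, among visit-1 responders.** Assumptions that are not in the documents:

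- every BCM responder would also respond to SCRM;
- relapse risk is r0 in these common responders, in either arm;
- relapse risk is r in the SCRM-only responders, whose share is 0.895 − 0.546 = 0.349;
- a visit-1 responder has either relapsed or is still responding at visit 6.

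Then:

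- SCRM recurrence = (0.546 × r0 + 0.349 × r)/0.895; BCM recurrence = r0.
- Sustained response over all randomised: SCRM = 0.895 − (0.546 × r0 + 0.349 × r); BCM = 0.546 × (1 − r0).

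| r0 | r | Recurrence, SCRM v BCM | Sustained response, SCRM v BCM |
|---|---|---|---|
| 10% | 10% | 10.0% v 10.0% | 80.55% v 49.1% |
| 10% | 20% | 13.9% v 10.0% | 77.1% v 49.1% |
| 10% | 40% | 21.7% v 10.0% | 70.1% v 49.1% |
| 10% | 60% | 29.5% v 10.0% | 63.1% v 49.1% |
| 20% | 10% | 16.1% v 20.0% | 75.1% v 43.7% |

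The third row in full: (0.0546 + 0.1396)/0.895 = 0.1942/0.895 = 21.7%, and 0.895 − 0.1942 = 70.1%.

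In 200,000 simulated trials of that row at 48 per arm, recurrence was numerically higher with SCRM in 91%. It was nominally significantly worse (chi-square, two-sided 0.05) in 22%. Sustained response was higher with SCRM in 98%. These percentages follow from choosing 40% against 10%.

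**Reading 3: all visit-6 cureless cases over visit-1 responders.** Assume that visit-1 non-responders stay cureless, with the third-row risks. SCRM is (0.105 + 0.1942)/0.895 = 33.4% and BCM is (0.454 + 0.0546)/0.546 = 93.2%. The ranking is not reversed here.

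**Sensitivity to the response inputs.** The printed efficacy rate subtracts cureless cases. If the planned 89.5% and 54.6% were produced that way, each equals 2p − 1. The responder shares are then (1 + 0.895)/2 = 94.75% and (1 + 0.546)/2 = 77.3%, and the SCRM-only share is 17.45%. With 10% and 40%, SCRM recurrence is (0.0773 + 0.0698)/0.9475 = 15.5% v 10.0%. Sustained response is 80.0% v 69.6%. The ranking still reverses, by less.

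**The case against.** A reader might infer that the recurrence formula as printed can make the better technique look worse. The documents do not support that. With all counts at visit 6 it is a non-response odds, which cannot reverse the ranking, and Reading 3 shows no reversal under the assumptions used. Reversal needs the numerator to follow the verbal definition and the denominator to be visit-1 responders. That reading is reasonable, because symptoms can reappear after treatment only if they had first abated, but the formula does not state it.

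A reader might also infer that the week-24 durability claim rests on this rate alone. It does not: the efficacy rate is also calculated at visit 6, over all patients. Nor is a significance test of recurrence written down. The Statistical Analysis section speaks of rates in general, so such a test is implied at most.

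The size is open too. No relapse risk of 20%, 40% or 60% has a source in the documents. The Introduction reports an efficacy rate of 94.74% and then 89.47% at 3 months, in patients with radiculopathy. The planned 89.5% matches the later figure and may already be net of relapse. The net loss there is (94.74 − 89.47)/94.74 = 5.6%, below every SCRM scenario in the table.

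These objections limit how large and how certain the effect is. They do not change the fact that the denominator is fixed in the text, is formed after randomisation, and is expected to differ greatly between the arms. The literal reading escapes the selection problem only because it does not measure recurrence.

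**Conclusion.** The concern holds in a conditional form. If recurrence is counted among initial responders, a between-arm comparison is not protected by randomisation and can disagree with the all-randomised result. Under the assumed 10% and 40% it gives 21.7% v 10.0% against SCRM, while sustained response is 20.9 points in its favour (0.349 × 0.60). Equal risks give no bias, and lower risk in the extra responders turns it round (16.1% v 20.0%). Direction and size therefore cannot be known from the documents, and it should not be said that the rate will mislead.

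If the formula is instead applied literally at visit 6, it gives 11.7% v 83.2% at the planned rates. The ranking is then safe, but the figure repeats non-response under another name and can exceed 100%. Under neither reading is it a sound basis for comparing durability.

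**What to change.** 1. **Between-arm comparison.** Define sustained response as clinical cure or improvement at both visit 1 and visit 6. Divide by the number randomised in each arm, as a plain proportion with no subtraction of cureless cases. Report the risk difference with its confidence interval.
2. **Descriptive figure.** Report recurrence per arm as visit-1 responders who meet the verbal definition by visit 6, divided by visit-1 responders, with no P value or superiority statement. This replaces the printed formula.

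Response at visit 6 must be required. Absence of recurrence is not enough. A patient whose NRS goes from 8 to 2 to 7 improves at visit 1 (75% decrease) and is cureless at visit 6 (1/8 = 12.5% decrease). Yet this patient has no recurrence by the verbal definition, because 7 is below 8.

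The cost is about one sentence each in Efficacy Rate and Statistical Analysis. Table 1 already schedules the efficacy evaluation at visits 1 and 6, and symptoms at every visit, so no new data are needed. Recruitment has begun, so the change should be documented, with ethics approval where the protocol requires it, before the statistician is unblinded.

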#### Secondary Outcomes

##### Severity of Neck Pain (VAS)

The VAS score will be used to evaluate the severity of neck pain in all participants [22]. The VAS score sheet consists of a horizontal 100-mm line with “painless” and “extremely painful” end points. Patients select a point on the line segment based on their own pain perception and draw a vertical line through that point to express the intensity of pain.

##### Severity of Vertigo (VSS-C)

The VSS-C scale has been used in many studies to evaluate the severity of vertigo and has shown high reliability and validity [23]. The VSS-C is a self-assessment scale consisting of 22 questions, with a score of 0-4 for each question. A total score of 0-33 points indicates mild vertigo, 34-67 points indicates moderate vertigo, 68-101 points indicates severe vertigo, and 102-136 points indicates extremely severe vertigo.

##### Imaging Changes of Cervical CT

All participants will undergo cervical CT examination at visits 0, 1, and 6. Two radiologists will measure the distance from the lateral mass of the atlantoaxial joint to the dentate process and the distance from the axis to the midline of the spinous process. Each radiologist will measure each image 3 times, and the average of the 6 outcomes will be taken as the final result. The improvement rate will then be calculated based on the results. The calculation formula is as follows:

Improvement rate = ([distance at pretreatment – distance after treatment] / distance at pretreatment) 100

##### Cervical Mobility

A cervical inclinometer will be used to measure cervical mobility. The outcome assessor will measure and record the cervical angles of the patient in 6 directions: flexion, extension, left rotation, right rotation, left lateral bending, and right lateral bending [24]. The outcome assessor will take 3 measurements in each direction, and the average of the 3 values will be used as the final result.

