### Diagnostic Criteria

The diagnosis of AJS is based on the Diagnostic Criteria for Traditional Chinese Medicine and the International Classification of Diseases 11th Revision (ICD-11), and several aspects are considered. First, the patient has a history of neck strain or injury and has a long-term habit of working or living with a low head. Second, the clinical manifestations are mainly vertigo, dizziness, headache, and soreness in the neck. Third, the cervical movement is mainly limited to the left-right rotation of the atlantoaxial joint. When performing palpation, the muscle tension around the atlantoaxial joint increases or small blocky or strip-shaped muscle nodules are felt, which may induce or exacerbate dizziness or vertigo. Fourth, cervical X-ray or CT shows an asymmetrical gap between the lateral mass of the atlantoaxial joint and the odontoid process, with a difference of more than 2 mm, along with the misalignment of the axis of the spinous process relative to the midline of the spinous process.

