### SCRM Technique

The primary technological approach in SCRM involves applying pressure with the thumb on the spinous process, transverse process, or pedicle of the patient’s axis while simultaneously rotating the cervical spine in an effort to restore it to its original alignment. AJS is categorized into 8 distinct techniques, which are determined by the specific imaging characteristics of the atlantoaxial joint. Figure 2 shows the comprehensive classification of AJS according to X-ray findings. Each technique within these categories employs different SCRM methods. When there is a simple asymmetrical gap between the lateral mass of the atlantoaxial joint and the odontoid process, the spinous process of the axis remains aligned with the midline of the spinous process, yet the discrepancy in distance between the lateral mass of the left and right atlas and the dentate process is evident. If the left block displays a 2-mm greater distance compared with the right block, it falls under type A (left oblique type). Conversely, if the right block displays a 2-mm greater distance compared with the left block, it is classified as type B (right oblique type). When there is a simple misalignment of the axis spinous process relative to the midline of the spinous process, the distance between the lateral masses of the left and right atlas and the dentate process is either equal or exhibits a difference within a 2-mm range. However, the spinous process of the axis deviates from the midline of the spinal axis. If the spinous process of the axis is located at the left of the midline, it is classified as type C (left rotation type). Conversely, if the spinous process of the axis is located at the right of the midline, it is categorized as type D (right rotation type). The types can mix as follows: when type A merges with type C, it is referred to as type AC; when type A merges with type D, it is referred to as type AD; when type B merges with type C, it is referred to as type BC; and when type B merges with type D, it is referred to as type BD. The SOPs of SCRM according to the different types are presented below [18].

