**Figure 2 figure2:**
[figure not shown]
Comprehensive classification of atlantoaxial joint subluxation using X-ray. The green line indicates the distance between the lateral mass of the atlantoaxial joint and the odontoid process. The blue line indicates the axis line of the C2 spinous process. The yellow line indicates the midline of the spinous process. (A) Normal atlantoaxial joint; (B) Type A; (C) Type B; (D) Type C; (E) Type D; (F) Type AC; (G) Type AD; (H) Type BC; (I) Type BD.

For type A, the steps are as follows. First, the patient assumes a seated position, while the medical therapist stands behind the patient on the left side. The therapist’s left hand supports the patient’s forehead, specifically positioning the right thumb at the left transverse process of the patient’s axis. The remaining 4 fingers of the therapist’s right hand rest gently on the right side of the patient’s neck, resulting in a forward flexion of the patient’s neck by approximately 10°. Second, the therapist subsequently alters the position of their left hand, placing it on the patient’s right chin nodule, while maintaining the unchanged posture of the right hand. This adjustment allows the therapist to rotate the patient’s neck to its maximum range of active movement. Third, the therapist’s left hand persists in applying force to achieve the maximum range of passive movement in rotating the patient’s neck, while the right thumb maintains a fixed position. The patient is instructed to relax their neck. Subsequently, the left hand momentarily intensifies the force of left rotation, while the right thumb applies pressure to the transverse process in a rightward direction. This maneuver often elicits an audible “click” sound emanating from the neck, accompanied by a subtle sliding sensation beneath the therapist’s right thumb, and the procedure is considered concluded.

For type B, the therapist stands behind the patient’s right side, and the therapist’s right hand supports the patient’s forehead, specifically positioning the left thumb at the right transverse process of the patient’s axis. The remaining steps are the same as those for type A, except that they are all performed in the opposite direction.

For type C, the operation steps are the same as those for type A, while the right thumb of the therapist is fixed at the left spinous process of the patient’s axis.

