### Limitations

For classification, AJS has been divided into 8 types. For the different types, the SCRM techniques are different, while the BCM techniques are the same. As the incidence rate of AJS is not high, it may be difficult to recruit patients with each type of AJS, who meet the statistical requirements, in a limited time. Therefore, we will not separate the different AJS types, but instead combine them to observe the difference in efficacy between SCRM and BCM. In the future, we will further extend our project timeline and recruit as many subjects as possible for each type of AJS, so that efficacy analysis can be conducted for different types of AJS.

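### Rotation is kept as separate left and right angles while mirror-image AJS types are pooled; if restriction is one-sided, the mobility endpoint loses power, though it is not biased

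*Protocol article*

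**What the plan says.** - **Measurement.** Cervical Mobility lists "6 directions: flexion, extension, left rotation, right rotation, left lateral bending, and right lateral bending". It continues: "The outcome assessor will take 3 measurements in each direction, and the average of the 3 values will be used as the final result". It defines no combined arc and no coding by affected side.
- **Types.** SCRM Technique defines types by side on imaging: A and B are the left and right oblique types, C and D the left and right rotation types, and four types are mixtures. For type C: "If the spinous process of the axis is located at the left of the midline, it is classified as type C (left rotation type").
- **Treatment direction.** The type A procedure ends in a left rotation. The type B steps repeat those of type A, "except that they are all performed in the opposite direction". Type C follows A and type D follows B.
- **Comparator.** BCM is the same for every type.
- **Pooling.** Limitations states: "we will not separate the different AJS types, but instead combine them to observe the difference in efficacy between SCRM and BCM".
- **Restriction.** Diagnostic Criteria says "the cervical movement is mainly limited to the left-right rotation of the atlantoaxial joint", without saying whether one or both directions are restricted in a given patient.
- **Analysis.** Statistical Analysis lists change in cervical mobility among the secondary analyses, names an analysis of variance within groups for repeated measurements, and sets a one-sided level of .05 for the superiority test.

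**The concern.** SCRM is directed by the side of the lesion and BCM is not. If targeting brings a benefit, it could show mainly in rotation toward the restricted side. Averaging left rotation over a pooled arm then mixes patients whose left rotation was restricted with patients whose left rotation was free, and right rotation has the same problem. A gain on the restricted side is split between two averages, each showing only part of it. A null mobility result could then reflect how sides were coded, not the treatment. The stated within-group analysis does not help, because it neither realigns the sides nor compares the groups.

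**Working it through.** The article gives no effect size, SD or power for mobility, so there is no stated figure to reproduce. Its 48 per group belongs to the primary efficacy rate and serves here only as an input.

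**Inputs from the article**
- 48 per group with up to 20% dropout (Sample Size): 48 × 0.8 = 38.4, so about n = 38 per group.
- One-sided α = .05 (Statistical Analysis), z = 1.645.

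**Assumptions, not in the article**
- d: the between-group difference in change on the restricted side, in SD units of change; range 0.5 to 1.0.
- q: the share of patients whose restricted side is the direction analysed; 0.5 as base case.
- f: the fraction of d also gained on the other side; 0 as base case.
- ρ: the correlation between left and right change; 0 to 0.5.

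**Step 1: aligned to the restricted side.** Power = Φ(d / √(2/n) − 1.645), with √(2/38) = 0.2294. For d = 0.5: 0.5/0.2294 − 1.645 = 0.534, giving 70%.

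**Step 2: fixed left or right direction.** With f = 0, the mean effect is q·d and the SCRM-arm variance is 1 + q(1−q)d². Power = Φ(q·d / √([2 + q(1−q)d²]/n) − 1.645). For d = 0.5 and q = 0.5: 0.25 / √(2.0625/38) = 0.25/0.2330 = 1.073; 1.073 − 1.645 = −0.572, giving 28%.

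**Step 3: total rotation.** The effect is d and the SD is √(2(1+ρ)).

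| d | Aligned to restricted side | Fixed direction, 50:50 mix | Total rotation, ρ = 0.5 to 0 |
|---|---|---|---|
| 0.5 | 70% | 28% | 35% to 46% |
| 0.7 | 92% | 43% | 55% to 70% |
| 1.0 | 99.7% | 66% | 81% to 92% |

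**Step 4: relaxing the assumptions at d = 0.7**
- If the other side also gains f·d, with a 50:50 mix, fixed-direction power is 59% (f = 0.25), 73% (f = 0.5), 85% (f = 0.75) and 92% (f = 1). At f = 1 the loss is gone.
- With a 75:25 side mix and f = 0, the majority direction keeps 72%. The minority direction has 0.175 / √(2.0919/38) − 1.645 = −0.90, about 18%.

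**Step 5: cost of the change if restriction is two-sided.** If both directions gain d, total rotation has a standardised effect of 2d/√(2(1+ρ)) = d·√(2/(1+ρ)), which is never below d. At d = 0.5 and ρ = 0.5 this is 0.577: 0.577/0.2294 − 1.645 = 0.87, giving 81% against 70% for one direction alone.

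**The case against.** The strongest objection is that the key premise is not in the article. Diagnostic Criteria speaks of left-right rotation, which can be read as restriction both ways. The type labels describe imaging geometry, and nothing ties a type to a restricted direction of movement. Treatment does not map cleanly to one side either: type AD receives the type A steps and then the type D steps, which run in opposite directions, and BCM may be given on both sides. All of this stands, so the loss is conditional.

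A second objection is that Cervical Mobility only describes measurement, and an analysis plan not shown could derive a total or affected-side angle. That is possible. But the section does fix the per-direction mean as the result, Limitations fixes the pooling, and the only repeated-measures analysis named is within groups. The imaging outcome, by contrast, is given a derived measure.

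Three stronger readings are tempting and are not supported:
- **Bias between groups.** Randomization balances left and right on average, so this is dilution only.
- **That the endpoint will miss a real effect.** The article supplies no effect, SD, side mix or pattern of restriction, so no single power figure can be attached to it.
- **The same fault in lateral bending.** No section describes sided loss of that movement.

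**Conclusion.** The point holds as a conditional loss of power on a secondary endpoint. Absolute left and right angles, pooled mirror-image types and direction-specific SCRM are all in the text; one-sided restriction is an assumption. Under it, with an even mix and no gain on the other side, each fixed direction carries half the restricted-side effect, and power falls from about 70% to 99.7% down to about 28% to 66% over d = 0.5 to 1.0. The loss shrinks as the other side also gains, and is zero if both sides are equally restricted and respond equally. An uneven mix protects one direction at the expense of the other. The primary outcome and the sample size are unaffected. This is a low-priority improvement, worth making because it costs almost nothing.

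**What to change.** In Cervical Mobility and Statistical Analysis:

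1. Name total rotation (left plus right) as the leading mobility measure. It needs no decision about the affected side.
2. Name rotation on the side more restricted at baseline as supportive, with a rule for ties. Choosing the side by the baseline angle works for all eight types, including the mixed ones. Any regression to the mean from that choice is expected to be equal in the two randomized arms.
3. Compare each measure between groups with its own baseline angle as covariate, in place of relying on the within-group analysis.
4. Keep the six raw angles as descriptive tables, and leave lateral bending as it is.

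The cost is a recoding of angles that Table 1 already schedules at every visit. Total rotation recovers only part of the lost power if restriction is one-sided (Step 3), which is why the restricted side is reported beside it. If restriction is two-sided, essentially nothing is given up. The choice should be written down before the statistician is unblinded, so that it cannot look like a selection among six angles after the results are seen.
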